## PallSoft- PALLiative radiotherapy in symptomatic pelvic SOFT tissue tumors

A randomized, open-label, multicenter, national, parallel-arm non-inferiority phase III trial investigating whether palliative radiotherapy delivered in 1-2 fractions is non-inferior to palliative radiotherapy delivered in 5 fractions with respect to change in target symptom intensity in patients with pelvic soft tissue tumors.

### Number of arms:

Two

### Masking:

No masking

### Primary Health Measurement:

PROM (Patient Reported Outcome Measures)

### Disease:

Gastrointestinal, urological or gynecological cancer

**Study phase:**

III

**Date**

## Protocol Amendment Summary of Changes Table

| Version | Date           | Section updated                                                                                       | Summary of changes                                                                                                                                                                                                                                                                                                  | Reason for change                                                                                                                                         |
|---------|----------------|-------------------------------------------------------------------------------------------------------|---------------------------------------------------------------------------------------------------------------------------------------------------------------------------------------------------------------------------------------------------------------------------------------------------------------------|-----------------------------------------------------------------------------------------------------------------------------------------------------------|
| 1.0     | 21.03.2023     |                                                                                                       | NA                                                                                                                                                                                                                                                                                                                  | Initial protocol                                                                                                                                          |
| 2.0     | 13.10.2023     | Contact details

3
5
5.1
6.8 and 8.1
2.1.3, 2.2.2.1, 2.3,
8.4.2, 8.8
2, 8.2.1 | New head of department (sponsor)
New project leader
Project management group added
Clarification objectives/endpoints
Updated recruitment procedure
Updated inclusion criteria
Updated concomitant medications
Added exploratory endpoint (hypoxia biomarkers)

Narrative clarifications | Feedback from Regional Committee for Medical Research Ethics South East Norway (REC South East)

Discussions in the study group |
| 2.1     | .06.02.2024    | 5
8.1
8.4.2
8.2.1.1                                                                          | Updated recruitment procedures
Updated baseline status
Updated planned procedures
Elaborative information                                                                                                                                                                                                  | Feedback from REC South East

Discussions in the study group                                                                                    |
| 2.2     | April/May 2024 | 9.5, 9.6

1.1, 2.1.3, 2.2.2.1, 3, 8.4.2

5                                                | Statistical analyses updated/elaborated
Fig.1 updated according to SoA
Exploratory endpoints updated
Title page updated
Narrative clarifications
Recruitment procedure updated                                                                                                                       | Discussions with study statistician
Discussions in study group

Feedback from REC South East                                                 |
| 2.3.1   | 12.07.2024     | 5                                                                                                     | Recruitment procedure updated                                                                                                                                                                                                                                                                                       | Feedback from REC South East                                                                                                                              |

|       |  |                                                                     |                                                                                                                                  |                                      |
|-------|--|---------------------------------------------------------------------|----------------------------------------------------------------------------------------------------------------------------------|--------------------------------------|
|       |  | 1.2
1.2, 2.3.1, 3, 4.1,
8.2.1, 4.1
6.3
1.2, 5.1, 8.3.5, | SoA clarified
Assessment PROM at 6 months
added. Fig.1 clarified
Updated randomization stratification
WOCBP updated  | Discussion in study
group         |
| 2.3.2 |  | 8.2.1
1.2, 6.2                                                   | NRS baseline as demographic
variable
Narrative clarifications
Updated Contact Details
Fig.1 updated (clarifications) | Discussion in study
group         |
| 2.4   |  | 5.1
1.2, 2.1, 3, 4.1,
Fig.1, 8.2
6.2, 8.1, 8.5.1           | Inclusion criterium added
PROMS at 8 weeks added

Narrative clarifications                                              | Discussion in study
group and DMC |

## **1. Protocol Summary**

### **1.1. Synopsis**

#### **Protocol Title:**

PallSoft- Palliative radiotherapy in symptomatic pelvic soft tissue tumors

A randomized, open-label, national, parallel-arm non-inferiority phase III trial investigating whether palliative radiotherapy delivered in 1-2 fractions is non-inferior to palliative radiotherapy delivered in 5 fractions with respect to change in target symptom intensity in patients with pelvic soft tissue tumors.

#### **Background:**

Studies and clinical practice have proven palliative radiotherapy to provide efficient symptom relief in patients with symptomatic pelvic soft tissue tumors. However, studies are mainly retrospective and difficult to compare due to a variety of radiotherapy fractionation schedules used, and they lack data on patient-reported quality of life (QoL). Consequently, no recommended standard of care is currently established in Norway. Several regimens are employed with variations in both number of fractions and total radiation dose (indicated in gray [Gy]).

In 2009–2015, the prospective, phase II, non-randomized PallRad study was conducted at several radiotherapy centers in Norway, and investigated the patient-reported symptomatic effect of palliative radiotherapy in participants with rectal and prostate cancer. The study proved radiotherapy to provide efficient symptom palliation, and displayed feasibility in addressing this particular topic in a multicenter setting.

A randomized trial designed to provide evidence of the optimal radiotherapy schedule in patients with symptomatic pelvic soft tissue tumors is highly warranted. Given the limited life expectancy of palliative patients, a short-course radiotherapy schedule would be preferable provided efficient symptom relief and good health-related quality of life.

#### **Study rationale:**

The main objective is to assess whether 1–2 fractions of 8 Gy can provide non-inferior patient-reported target symptom relief compared to 5 fractions of 5 Gy in patients with symptomatic pelvic soft tissue tumors. The target symptom is defined as one of the following five symptoms related to the irradiated tumor: pain, bleeding, bowel dysfunction, lower urinary tract dysfunction, and vaginal dysfunction

**Objectives, Endpoints, and Assessments:****Primary objective**

*Assess whether 1-2 fractions of 8 Gy is non-inferior to 5 fractions of 5 Gy with respect to target symptom relief.*

Endpoint: Change in the average (last 24 hours) patient-reported target symptom intensity from baseline assessed after 12 weeks of follow-up

Assessment: Numerical Rating Scale (NRS) score (0-10)

**Secondary objectives**

*To assess the efficacy of 1-2 fractions of 8 Gy compared to 5 fractions of 5 Gy with respect to:*

- Physician-reported toxicities

Endpoint: Bladder and bowel toxicity after 4, 12 and 52 weeks of follow-up

Assessment: Common Terminology Criteria for Adverse Events (CTCAE) v 5.0

- Survival

Endpoint: Overall survival (OS) assessed at the end of study

**Exploratory objectives**

*1. To assess the efficacy of 1-2 fractions of 8 Gy compared to 5 fractions of 5 Gy with respect to:*

- Patient-reported QoL

Endpoint: Change in QoL from BL after 4, 8, 12 and 26 weeks of follow-up

Assessment: European Organization for the Research and Treatment of Cancer Quality of Life Questionnaire-Core15 Palliative (EORTC QLQ-C15 PAL)

- Physician-reported toxicities

Endpoint: All relevant toxicities after 4, 12 and 52 weeks of follow-up

Assessment: CTCAE v 5.0

- Patient reported symptomatic effect

Endpoints: Change in target symptom intensity from baseline after 4, 8 and 26 weeks of follow-up, and changes in intensity of symptoms related to the irradiated tumor other than target symptom (within the five predefined categories) from baseline after 4, 8, 12 and 26 weeks of follow-up

Assessment: NRS score 0-10

- Patient satisfaction

Endpoint: Assessment of patient satisfaction after 4, 8, 12 and 26 weeks of follow-up

Assessment: Patient Global Impression of Change (PGIC)

*2. To explore prognostic models for patient classification*

Endpoint: Correlation between prognostic scores assessed at baseline and overall survival

Assessment: Glasgow Prognostic Score (GPS), LabPS- score and LabBM- score

*3. To explore clinical factors as explanatory response variables*

Endpoint: Correlation between clinical factors and symptomatic response

Assessment: Baseline registration of clinical factors from medical records

*4. Assess hypoxia biomarkers on medical images and biopsies that are previously acquired for diagnosis or treatment, and explore their potential as explanatory response variables in individual patients.*

Endpoint: Correlation between hypoxia biomarkers and symptomatic response

Assessment: Hypoxic fraction assessed by Consumption and Supply-based Hypoxia (CSH)-imaging on MRI (Magnetic Resonance Imaging) and hypoxia-activated protein and gene expression assessed by molecular analyses on tumor biopsies

*5. Assess PD-L1 (Programmed Death-Ligand1)-status in biopsies previously acquired for diagnosis or treatment, and explore potential as explanatory response variable.*

Endpoint: Correlation between PD-L1-status and symptomatic response

Assessment: PD-L1 expression level (all cells) assessed by immunohistochemistry

*6. Compare the health-economic aspects in the two study arms regarding*

- *Patient-reported QoL*

Endpoint: Change in QoL compared to baseline assessed after 4, 8, 12 and 26 weeks

Assessment: EQ-5D-5L (5 Level-EuroQol-5 Dimensions)

- *Health service costs*

Endpoint: Difference in costs related to attendance at the radiotherapy unit, transportation and hospital submissions

Assessment: Registration of costs from medical records

**Overall Design:**

This prospective, randomized, open-label, national, parallel-arm non-inferiority phase III study is designed to establish non-inferiority of radiotherapy with 1-2 fractions of 8 Gy to 5 fractions of 5 Gy with respect to patient-reported symptomatic relief. Patients in arm A will initially receive a single fraction of 8 Gy. If unsatisfactory symptomatic response after 4 weeks of follow-up, a

second fraction *may* be offered if at least one of the following two predefined criteria are met: 1) less than a 2 point improvement on the NRS-scale and/or 2) initial symptomatic effect, but rapid deterioration of symptoms, [see Section 4.3.1](#)). Patients in arm B will receive five consecutive fractions of 5 Gy. The study population includes patients with gastrointestinal, urological or gynecological cancers considered candidates for palliative radiotherapy, and with expected survival over 12 weeks. Eligible patients identified in the screening period will be randomized to either arm A or arm B with an allocation ratio of 1:1 after collection of a signed informed consent. Assessment of endpoints will be performed at 4, 8 12 (primary endpoint) and 52 weeks after the radiotherapy is completed. Survival data will be collected and assessed at the end of the study.

**Brief Summary:**

The purpose of this study is to investigate whether palliative radiotherapy delivered 1-2 fractions of 8 Gy is non-inferior to palliative radiotherapy delivered in 5 fractions of 5 Gy with respect to change in patient-reported symptom intensity in patients with pelvic soft tissue tumors originating from either gastrointestinal, urological or gynecological cancer. Patients will define a target symptom as their main complaint according to study-specific predefined categories (pain, bleeding, bowel dysfunction, lower urinary tract dysfunction or vaginal dysfunction).

Patients will be randomly assigned to radiotherapy intervention with either 1-2 fractions of 8 Gy or 5 fractions of 5 Gy. Patients entering the study must be considered as candidates for palliative radiotherapy, and have a target symptom intensity at baseline of minimum 4 points on the NRS, which ranges from 0-10 with 0 indicating no symptom intensity and 10 indicating the worst symptom intensity imaginable.

For patients randomized to 1-2 fractions of 8 Gy, the second fraction will be offered if predefined criteria for unsatisfactory symptomatic response are met, assessed at the 4-week follow-up ([see Section 4.3.1](#)).

Assessment of endpoints will be performed at 4, 8, 12 (primary endpoint), 26 and 52 weeks after the radiotherapy is completed. Assessments include patient-reported evaluation of symptom intensity (NRS), QoL, overall patient satisfaction and physician-reported toxicities. Subjects will be followed with respect to overall survival until death, or censoring, defined as either loss to follow-up, study withdrawal or end of study.

The radiotherapy planning and deliverance, and the study-specific follow-up visits (attendance or by telephone) will be performed at the patients' local radiotherapy unit. Additional follow-up visits related to the patients' cancer disease will be performed at their local cancer department, and will be according to the institutional practice, independent of study inclusion.

Patients will be included over a period of 2-4 years with a maximum follow-up at study closure (overall survival).

The results of this study may contribute to the establishment of standard treatment recommendations, both nationally and internationally. Both interventions are currently being used in clinical practice, which will facilitate the implementation of study results.

**Number of Participants:**

A maximum of 200 patients will be randomly assigned to study intervention to achieve a per protocol (PP) population of 146 patients

**Data Monitoring/Other Committee:**

The study is organized with a Data Monitoring Committee (DMC) and Steering Committee

## 1.2. Schedule of Activities (SoA)

| Procedure                                                         | Up to 28 days |                | Intervention Period [1 or 5 weekdays] |    |    |    |    | Follow-up a |                       |                                    |                        |                         |                         | Notes                          |
|-------------------------------------------------------------------|---------------|----------------|---------------------------------------|----|----|----|----|------------------------|-----------------------|------------------------------------|------------------------|-------------------------|-------------------------|--------------------------------|
|                                                                   | Screening     | Preparation    | D1                                    | D2 | D3 | D4 | D5 | 1 week
+/- 3 days   | 4 weeks
+/- 4 days | 8 weeks
+/- 4 days b | 12 weeks
+/- 7 days | 26 weeks
+/- 2 weeks | 52 weeks
+/- 4 weeks |                                |
| Informed consent                                                  | X             |                |                                       |    |    |    |    |                        |                       |                                    |                        |                         |                         | Section 10.1.2 |
| Inclusion and exclusion criteria                                  |               | X              |                                       |    |    |    |    |                        |                       |                                    |                        |                         |                         | Section 5      |
| Demography and medical history                                    | X             |                |                                       |    |    |    |    |                        |                       |                                    |                        |                         |                         | Section 8.1    |
| ECOG performance status                                           | X             |                |                                       |    |    |    |    |                        | X                     |                                    | X                      |                         |                         | Section 8.3.3  |
| Pregnancy test (WOCBP)                                            |               | X c |                                       |    |    |    |    |                        |                       |                                    |                        |                         |                         | Section 8.3.5  |
| Local laboratory tests (albumin, CRP, hemoglobin, platelets, LDH) |               | X              |                                       |    |    |    |    |                        |                       |                                    |                        |                         |                         | Section 8.4.1  |
| Randomization                                                     |               | X d |                                       |    |    |    |    |                        |                       |                                    |                        |                         |                         | Section 6.3    |
| CT for radiotherapy planning                                      |               | X              |                                       |    |    |    |    |                        | (X) k      |                                    |                        |                         |                         | Section 6.2    |
| Cone beam CT (or kV/kV)                                           |               |                |                                       |    |    |    |    |                        | X k        |                                    |                        |                         |                         | Section 6.2    |

| Procedure                                  | Up to 28 days |             | Intervention Period [1 or 5 weekdays] |    |    |    |    | Follow-up a |                       |                                    |                        |                         |                         | Notes                              |
|--------------------------------------------|---------------|-------------|---------------------------------------|----|----|----|----|------------------------|-----------------------|------------------------------------|------------------------|-------------------------|-------------------------|------------------------------------|
|                                            | Screening     | Preparation | D1                                    | D2 | D3 | D4 | D5 | 1 week
+/- 3 days   | 4 weeks
+/- 4 days | 8 weeks
+/- 4 days b | 12 weeks
+/- 7 days | 26 weeks
+/- 2 weeks | 52 weeks
+/- 4 weeks |                                    |
| Intervention/treatment, arm A              |               |             | X                                     |    |    |    |    |                        | X bj       |                                    |                        |                         |                         | Section 6.1, 4.3.1 |
| Intervention/treatment, arm B              |               |             | X                                     | X  | X  | X  | X  |                        |                       |                                    |                        |                         |                         | Section 6.1        |
| NRS score target symptom                   | X             |             |                                       |    |    |    |    |                        | X                     | X                                  | X                      | X                       |                         | Section 8.2.1.1    |
| NRS score other symptoms                   | X             |             |                                       |    |    |    |    |                        | X                     | X                                  | X                      | X                       |                         | Section 8.2.1.1    |
| EORTC QLQ-C15 PAL                          |               | X           |                                       |    |    |    |    |                        | X                     | X                                  | X                      | X                       |                         | Section 8.2.1.2    |
| Patient Global Impression of Change (PGIC) |               |             |                                       |    |    |    |    |                        | X                     | X                                  | X                      | X                       |                         | Section 8.2.1.3    |
| EQ-5D-5L                                   |               | X           |                                       |    |    |    |    |                        | X                     | X                                  | X                      | X                       |                         | Section 8.2.3      |
| CTCAE v.5.0                                |               | X           |                                       |    |    |    |    |                        | X                     |                                    | X                      |                         | X                       | Section 8.3.2      |
| GPS                                        |               | X           |                                       |    |    |    |    |                        |                       |                                    |                        |                         |                         | Section 8.4.1      |
| LabBM score                                |               | X           |                                       |    |    |    |    |                        |                       |                                    |                        |                         |                         | Section 8.4.1      |
| LabPS score                                |               | X           |                                       |    |    |    |    |                        |                       |                                    |                        |                         |                         | Section 8.4.1      |

| Procedure                           | Up to 28 days |             | Intervention Period [1 or 5 weekdays] |    |    |    |    | Follow-up a |                       |                                    |                        |                         |                         | Notes                            |
|-------------------------------------|---------------|-------------|---------------------------------------|----|----|----|----|------------------------|-----------------------|------------------------------------|------------------------|-------------------------|-------------------------|----------------------------------|
|                                     | Screening     | Preparation | D1                                    | D2 | D3 | D4 | D5 | 1 week
+/- 3 days   | 4 weeks
+/- 4 days | 8 weeks
+/- 4 days b | 12 weeks
+/- 7 days | 26 weeks
+/- 2 weeks | 52 weeks
+/- 4 weeks |                                  |
| AE review                           |               |             | ←=====→                               |    |    |    |    | X h         | X h        | X k,h                   | X i         |                         | X i          | Section 8.5      |
| SAE review                          |               |             | ←=====→                               |    |    |    |    | X h         | X h        | X k,h                   | X i         |                         | X i          | Section 8.5      |
| Supportive medications c | X             |             |                                       |    |    |    |    |                        | X                     |                                    | X                      |                         |                         | Section 6.8, 8.1 |
| Radiotherapy record f    |               | X           |                                       |    |    |    |    |                        |                       |                                    | X                      |                         | X                       | Section 6.6, 8.1 |
| Administration g         |               |             |                                       |    |    |    |    | X                      | X                     | X k                     |                        |                         |                         | Section 8.2.3    |

Abbreviations: AE=Adverse Event, CT= Computed Tomography, CTCAE= Common Terminology Criteria Adverse Events, CRP= C-reactive protein, ECOG = Eastern Cooperative Oncology Group, EORTC QLQ-C15 PAL= European Organization for the Research and Treatment of Cancer Quality of Life Questionnaire-Core15 Palliative, GPS= Glasgow Prognostic Score, LDH=Lactate dehydrogenase, NRS=Numerical Rating Scale, SAE=Serious Adverse Event, WOCBP=Women of childbearing potential

a All follow-up is defined from the day of completed radiotherapy (arm A: D1, arm B: D5 or D6-10 if modifications, see Section 6.5)

b If a second fraction is offered (see [Section 4.3.1](#)), evaluation must be scheduled 4 weeks +/- 4 days after the second fraction is delivered,. For all other patients, evaluations must be scheduled 8 weeks +/- 4 days from baseline

c Within 72 hours before randomization

d Only if baseline NRS score of target symptom is available

e Including pain medication, tranexamic acid, anticoagulants, laxatives, antidiarrheal medication, antiemetics and steroids

f Radiotherapy treatment within the same planning target volume (PTV) (additional fraction after 4 weeks in arm A is not considered reirradiation)

g I.e. hospital submissions and coding record related to radiotherapy

h All AE ≥grade 3/SAE

i Only AE ≥grade 3/SAE with suspected causality with radiotherapy

j To be performed within 4 days after decision

k Only if second fraction is offered. See [Section 4.3.1](#)

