#### **8.5.1. Time Period and Frequency of Collecting AE and SAE Information**

All SAEs and AEs with CTCAE grade  $\geq 3$  will be collected from the start of study intervention until the 52 week follow-up visit as specified in the SoA ([Section 1.2](#)), and recorded in the eCRF. After the 4 week follow-up visit, only SAEs/AEs with CTCAE grade  $\geq 3$  with probable/definite causality with radiotherapy will be reported. For patients in arm A receiving a second radiotherapy fraction, all SAEs/AEs with CTCAE grade  $\geq 3$  will be reported until the 8 week follow-up.

Medical occurrences that begin before the start of study intervention, but after obtaining informed consent will be recorded as current medical history ([section 8.1](#)), and not as AEs.

All SAEs will be recorded and reported to the sponsor or designee immediately and under no circumstance should this exceed 24 hours, as indicated in [Appendix 3](#). The investigator will submit any updated SAE data to the sponsor within 24 hours of it being available.

Investigators are not obligated to actively seek information on AEs or SAEs after conclusion of the study participation. However, if the investigator learns of any SAE, including a death, at any time after a patient has been discharged from the study, and he/she considers the event to be reasonably related to the study intervention or study participation, the investigator must promptly notify the sponsor.

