### **9.2. Statistical Hypotheses**

The primary hypothesis is that a radiotherapy schedule of 1-2 fractions of 8 Gy provides non-inferior patient-reported symptomatic relief as a schedule of five fractions of 5, assessed 12 weeks after completed radiotherapy (see [Section 9.1](#) for definition of the non-inferiority margin). The lower bound of the 95% confidence interval of the difference in mean symptom intensity of arm A is therefore hypothesized to be above the non-inferiority margin of -1.

If non-inferiority regarding symptom relief, and comparable QoL, toxicities and OS can be proved 12 weeks after the intervention a short-course schedule with 1-2 fractions will be recommend as standard of care. If non-inferiority can be proven only 4 weeks after the intervention, a single fraction schedule will be recommend for patients with a very short life expectancy where palliative radiotherapy is considered reasonable.

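### The 8-week visit has two conflicting anchors, and all-cause AE/SAE collection runs to week 8 only in arm A patients given a second fraction

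*Protocol*

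**What the plan says.** **Visit clock.** Protocol section 1.2, footnote a: "All follow-up is defined from the day of completed radiotherapy (arm A: D1, arm B: D5 or D6-10 if modifications". The Brief Summary in the synopsis also places the 8-week assessment after radiotherapy is completed. Footnote b, attached only to the 8-week column, gives two other rules. After a second fraction, "evaluation must be scheduled 4 weeks +/- 4 days after the second fraction is delivered"; otherwise, "For all other patients, evaluations must be scheduled 8 weeks +/- 4 days from baseline". Footnote j times the second fraction: "To be performed within 4 days after decision". Section 4.1 puts the baseline evaluation between consent and the start of the intervention, and the SoA lists the baseline NRS under screening, in a block headed up to 28 days. Section 9.2 describes the primary endpoint as "assessed 12 weeks after completed radiotherapy".

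**AE window.** Section 8.5.1 collects grade 3+ AEs and all SAEs from the start of the intervention. After the 4-week visit it keeps only those "with probable/definite causality with radiotherapy will be reported". It then makes an exception that runs to the 8-week follow-up: "For patients in arm A receiving a second radiotherapy fraction, all SAEs/AEs with CTCAE grade" 3 or higher are reported. In the SoA, the 8-week AE and SAE review is done only if a second fraction is offered (footnotes h and k). Section 2.3 states the post-week-4 restriction without that exception. Section 9.5.5 limits safety analysis to tabulations of events and of subjects with events.

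**Causality.** After week 4, footnote i asks for events "with suspected causality with radiotherapy". Sections 2.3 and 8.5.1 ask for probable or definite causality.

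**The concern.** Sites book visits from the SoA footnotes. Two starting points for one visit mean that week-8 NRS, QLQ-C15-PAL, PGIC and EQ-5D-5L may be taken at different times since treatment, depending on which footnote a site follows and how long before D1 its baseline was.

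The AE issue is separate. The longer all-cause window exists only in arm A, and only in patients selected after randomization by poor or lost response. In a palliative population, grade 3+ events unrelated to radiotherapy will be common. A plain by-arm count therefore includes events in some arm A patients that would not have been recorded in the same weeks in arm B. The data monitoring committee evaluates safety when 70 patients have completed 12 weeks (section 10.1.4), so the problem arises before the final analysis.

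Two causality thresholds mean that the same late event is reportable under one section and not under another.

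**Working it through.** The plan gives no figure for this point, and the sample size is not involved. Days are counted with D1 as day 0.

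**1. Week-8 visit, second-fraction patients (arm A)**
- 4-week visit: 28 ± 4 = day 24-32.
- Second fraction 0-4 days after the decision: day 24-36.
- Visit 28 ± 4 days later: 24 + 24 = day 48 to 36 + 32 = day 68. Nominal: day 56-60.

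**2. Week-8 visit, all other patients**
- Arm A on footnote a's clock (D1): 56 ± 4 = day 52-60, nominal 56. The nominal gap to step 1 is 0-4 days.
- Footnote b with baseline = D1: the same days for arm A. For arm B, with D5 on day 4, this is 48-56 days after the end of treatment, where footnote a would give 52-60.
- Footnote b with baseline 28 days before D1 (the longest lead in the SoA): 52 - 28 = day 24 to 60 - 28 = day 32. This is exactly the 4-week window for one-fraction arm A patients. For arm B it is 20-28 days after D5.
- With a 14-day lead, the visit falls on day 38-46.

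**3. All-cause AE/SAE window, measured from D1**
- Arm A, one fraction: 28 days.
- Arm A, second fraction: about 56-60 days.
- Arm B: 4 + 28 = 32 days.

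The share *s* receiving a second fraction is not given, so it is an assumption here. Mean arm A window = 28(1 - *s*) + (56 to 60)*s*.

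| *s* | Arm A mean (days) | Ratio to arm B (32 days) |
|---|---|---|
| 10% | 30.8-31.2 | 0.96-0.98 |
| 30% | 36.4-37.6 | 1.14-1.18 |
| 50% | 42-44 | 1.31-1.38 |

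The means are equal at *s* = 4/28 = 14% (56-day window) or 4/32 = 12.5% (60-day window).

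**4. What this does to a by-arm table**

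Assume the same constant hazard in both arms and a 20% risk of at least one event in four weeks. The eight-week risk is 1 - 0.8² = 36%. Arm A then shows 0.20(1 - *s*) + 0.36*s*:
- *s* = 10%: 0.180 + 0.036 = 21.6%
- *s* = 30%: 0.140 + 0.108 = 24.8%
- *s* = 50%: 0.100 + 0.180 = 28.0%

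Arm B shows 20% if its window is treated as four weeks. Counting its treatment days as well, it shows 1 - 0.8^(32/28) = 22.5%. At *s* = 30% the spurious excess in arm A is therefore 4.8 points, or 2.3 points on the stricter count. At *s* = 10% the stricter count slightly favours arm A (21.6% against 22.5%).

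**The case against.** The best defence is that the longer AE window is deliberate: it gives four weeks of all-cause reporting after each course, which is sensible safety practice. That stands as a reason to collect the data, but not as a reason to compare raw totals between arms over unequal windows. It is also fair that a week-4 cut of the tables could be set in the SAP, that the extra events usually count against the experimental arm and so do not flatter it, and that week-8 PROMs are exploratory. Footnote b's wording may well be a slip for D1 or end of treatment. If so, the visit shift is a few days; the day 24-32 figure needs the most extreme reading of baseline.

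Three stronger readings are tempting, and the documents do not support them.
- *The arms are not compared over the same time in general.* Footnote b governs only the 8-week column. The 12-week primary endpoint, CTCAE at 4, 12 and 52 weeks, the 26-week PROMs and overall survival carry no second-fraction exception.
- *In second-fraction patients the primary visit moves to 12 weeks after that fraction*, that is 24 + 84 - 7 = day 101 to 36 + 84 + 7 = day 127. Footnote a fixes arm A's completion day at D1, which gives 84 ± 7 = day 77-91. Section 4.3.1 does use completed radiotherapy for the time after the second fraction, so a clarifying sentence is worthwhile, but this is not the likely reading.
- *The cost row counts extra all-cause admissions in arm A.* Footnote g limits that row to radiotherapy-related admissions and coding. Further radiotherapy in the same volume is recorded to week 52 in both arms (section 6.6).

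**Conclusion.** Three defects stand. First, footnotes a and b give conflicting anchors for the 8-week visit. The effect runs from 0-4 days nominally, if baseline means D1, to a visit coinciding with the 4-week one, if baseline is 28 days before D1. It touches exploratory week-8 PROMs only. Second, all-cause grade 3+ AEs/SAEs are collected over about 56-60 days in second-fraction arm A patients, against about 28 days in one-fraction patients and 32 in arm B. Simple tabulations by arm therefore differ through window length alone. The size depends on a second-fraction share and a background event risk that the protocol does not state; 24.8% against 20-22.5% is an illustration under the assumptions above, not a forecast. Third, the post-week-4 causality threshold differs between footnote i and sections 2.3 and 8.5.1, and section 2.3 omits the second-fraction exception. The causality mismatch applies to both arms alike. The primary test and the sample size are unaffected. The corrections are worth making because they are cheap, and because an analysis plan cannot re-time visits or recover events that were never collected.

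**What to change.** 1. In footnote b, replace the baseline anchor for patients without a second fraction with footnote a's anchor, the end of the initial course. Add a sentence to section 9.2 that the 12-week visit is counted on footnote a's clock.
2. Compare the arms on all-cause grade 3+ AEs/SAEs over a common window, using events to week 4 in all patients. Tabulate later all-cause events in second-fraction patients separately. Stating whether that window starts at D1 or at the end of the initial course would settle the remaining four-day difference.
3. Alternatively, collect all-cause events to week 8 in everyone by adding an AE question to the week-8 PROM contact that already exists. For patients already past that visit, only the week-4 comparison is available.
4. Reconcile the causality term and the second-fraction exception across footnote i, section 2.3 and section 8.5.1.

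Items 1, 2 and 4 are text edits in one amendment, plus a line in the table specifications. Item 3 adds an eCRF field and a small burden on frail patients; it is optional if item 2 is adopted.
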